## Rationale for the Study

Adding Vacc-4x immunizations to ART could potentially reduce virus replication further by removing infected cells and thereby act to slow down the disease progression. Thus, by administering Vacc-4x to subjects who are clinically stable on ART, immune responses against HIV p24 should be boosted leading to improved health status.

In the previous studies with Vacc-4x it has been used as an intra-dermal administration using GM-CSF as an adjuvant. Since intra-dermal administration is dependent on trained health personal it is of interest to test a more simple administration route.

This study is to evaluate safety and immune response (T-cell response) after mucosal delivery (intranasal administration) of three different doses of Vacc-4x using Endocine as adjuvant to patients stable on ART.

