## Potential Risks and Benefits

Participants will provide important scientific information that may contribute to improved management of future HIV-positive subjects. Potential benefits for participants include a possible sustained improvement in the immune response to p24 and HIV. All patients will continue their regular ART regimen throughout the study and the study design does not involve scheduled ART interruption. Potential risks include the discomfort and inconvenience associated with the immunizations and the risk of known or unknown side effects of exposure to Vacc-4x given as intranasal administration with Endocine as adjuvant.

After intranasal administration the most common types of adverse events are expected to be related to local irritation of the nasal mucosa.

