5. For cryopreservation of PBMC to T cell response assays with optional samples for T cell response kinetics and optional assays on fresh blood samples. X, mandatory assay time points; x, optional time points pending on responsiveness.

During the Treatment Period, all subjects will remain on their ART and receive four immunizations at Weeks 1, 2, 3 and 4, with Vacc‑4x including Endocine as adjuvant.

The study is sequential, meaning that the first five subjects receive either adjuvant only (two patients) or the lowest dose (three patients) 80 µg Vacc-4x together with Endocine (given as 40 µg Vacc-4x as 150µl Endocine solution in each nostril). If the safety evaluation after two weeks is ok, the next dose level will be started, see Figure below:

[figure not shown]

##

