### Vaccine toxicity management

#### Administration site reactions

The following local reactions will be reported:

- Pain, tenderness, acute swelling or soreness at the application site (nose). The severity of pain or other reactions will be categorized as: None,’ ‘Mild’ (awareness of symptom but easily tolerated), ‘Moderate’ (discomfort enough to cause interference with usual activities), or ‘Severe’ (incapacitating with inability to work or do usual activity)

For administration site reactions judged to be life-threatening or severe, the investigational drug substance suppliers should be notified within 24 hours, and further vaccines should not be given to the subject prior to consultation with the suppliers.

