#### Systemic reactions

Systemic reactions will be graded according to the Division of AIDS Table for Grading Severity of Adult and Pediatric Adverse Events (see Appendix 16.1). The investigational drug substance suppliers should be contacted within 24 hours for any systemic Grade 3 or 4 reactions thought definitely, possibly, or probably related to treatment. Further vaccines should not be given subject prior to consultation with the investigational drug suppliers.

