### Dosage and administration of study drug

Vacc-4x is administered intranasal as a mixture of Vacc-4x peptides and the adjuvant Endocine.

The study includes four groups:

***A low dose group***: 80 µg Vacc-4x (20 µg pr. peptide) divided into two administrations;

40 µg Vacc-4x in 150 µl Endocine for each nostril.

***A medium dose group***: 400 µg Vacc-4x (100 µg pr. peptide) divided into two administrations;

200 µg Vacc-4x in 150 µl Endocine for each nostril.

***A high dose group***: 1200 µg Vacc-4x (300 µg pr. peptide) divided into two administrations;

600 µg Vacc-4x in 150 µl Endocine for each nostril.

***A zero dose group***: Only adjuvant divided into two administrations;

150 µl Endocine for each nostril.

The drug will be administered four times with one week interval; at week 1, week 2, week 3 and week 4.

A DTH test (Vacc-4x 400 µg intra-dermal) will be done at week 8.

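### The visible dosing hold after a severe reaction covers only the affected subject, and no visible rule makes others at that dose, or the next dose level, wait for the supplier consultation

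*Protocol*

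**What the plan says.** Section 4.1 of the Protocol describes a sequential design. The opening cohort is five subjects, two on adjuvant alone and three on 80 µg Vacc-4x with Endocine. The visible condition for moving up is "If the safety evaluation after two weeks is ok, the next dose level will be started". The sentence then points to a figure that is not shown.

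Section 5.4.1 (Vaccine toxicity management) sets two holds, each with a 24-hour contact to the suppliers:

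- **Administration-site reactions**, if severe or life-threatening: "further vaccines should not be given to the subject prior to consultation with the suppliers".
- **Systemic reactions**, when judged at least possibly treatment-related and of Grade 3 or 4: "Further vaccines should not be given subject prior to consultation with the investigational drug suppliers". Words are missing from this sentence.

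Table 2 in section 4.1 places the four doses on days 1, 8, 15 and 22. All four arms receive Endocine (sections 4.1 and 6.1.2). In the zero-dose arm it is given alone: "Only adjuvant divided into two administrations".

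**The concern.** Safety at three dose levels is the primary objective (section 3.1.1). In the earlier Vacc-4x studies, according to section 2.6, "it has been used as an intra-dermal administration using GM-CSF as an adjuvant", so both the route and the adjuvant are new for this product. Section 2.7 says that "the most common types of adverse events are expected to be related to local irritation of the nasal mucosa". A severe nasal reaction in one subject therefore carries information about everyone on the same dose and, because Endocine is common to all arms, possibly about everyone in the study.

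The protocol treats such a reaction as serious enough to withhold vaccine from that subject until the suppliers have been consulted. It does not visibly apply the same caution to the others to whom the answer matters. Followed as written, it would allow weekly doses to continue in other subjects, and the next level to start or stay open, while the question is still unresolved.

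**Working it through.** The protocol gives no figure on this point, so the check is mainly of the text.

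**Who must wait, by provision**

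- Section 4.1: the next level opens on an 'ok' two-week evaluation. The visible sentence does not define 'ok' or refer to section 5.4.1.
- Section 5.4.1, site reactions: the hold is explicitly on the affected subject.
- Section 5.4.1, systemic reactions: the word 'subject' is singular and no cohort or dose level is named. Single-subject scope is the natural reading, but it is an inference.
- Section 5.4: the investigator may withdraw an individual whose continuation would be harmful. This is discretionary.
- Section 9.1.6: serious events, and events causing permanent discontinuation, are reported to the suppliers. No dosing hold is set.
- Sections 12.3 and 12.9: the study may be stopped or suspended. Both are discretionary, and neither is tied to the consultation.

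None of these requires anyone other than the affected subject to wait.

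**Timing against the gate**

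The start of the two weeks is not stated. Assume that it is the first dose: 1 + 14 = day 15. The day-22 dose, and possibly the day-15 dose, then follow the evaluation. A severe reaction to either could arise when the next level is already open, and the visible text would hold only that subject.

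**Illustrative dose counts, first cohort**

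Inputs from section 4.1: 2 adjuvant-only + 3 at 80 µg = 5 subjects; doses on days 1, 8, 15 and 22. Assumptions: all start on the same day, and one subject reacts after dose 1 and is held. The length of the consultation is not stated.

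Doses given to others before the consultation ends = (number of others) × (dosing days passed).

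- Event at 80 µg: 3 − 1 = 2 others at that dose. Consultation over before day 8: 2 × 0 = 0. Over after the day-8 dose and before the day-15 dose: 2 × 1 = 2.
- Event in an adjuvant-only subject: 5 − 1 = 4 others receiving Endocine. On the same two timings: 4 × 0 = 0 or 4 × 1 = 4.

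With staggered starts and exact 7-day spacing, a consultation of under 7 days spans at most one dose per other subject, so the ranges 0 to 2 and 0 to 4 still hold. Section 7.3.2 prints a 1 in brackets beside days 8, 15 and 22. If that is a window of plus or minus one day, two doses could be as close as day 9 and day 14, that is 14 − 9 = 5 days apart. The staggered bound then needs a consultation of under 5 days.

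These counts concern other subjects only. They do not measure early opening of the next level: in this scenario the consultation ends before day 15, when the evaluation falls due on the assumption above.

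**The case against.** The strongest reply is that the protocol has layered controls and that an automatic hold is a matter of preference in a 24-subject pilot. The study is at one centre and the sponsor is the investigator, so one team sees every reaction. The suppliers hear within 24 hours and can suspend the study. The investigator can withdraw any individual. It would also be strained to call the evaluation 'ok' while a severe reaction is under mandatory consultation. All this is fair and lowers the practical risk. But these powers permit a wider hold without requiring one, whereas for the affected subject the protocol states a rule.

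The second reply is that the escalation scheme is in a figure that is not shown, and that the systemic sentence is damaged. This stands as a limit: only the site-reaction hold is explicit in its scope, and the figure may add a condition.

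Third, the counts rest on assumptions and start at 0, and prompt notice makes 0 plausible. This also stands. The case rests on the narrow rule, not on the counts.

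Fourth, a blanket halt of all arms would go too far. The site-reaction trigger has no relatedness test, so one severe nasal complaint of any cause could stop everything. In a single-blind study, pausing only one of two concurrently dosed groups could reveal allocation. Both objections are sound and shape the fix.

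A reader might infer that the protocol lets escalation proceed regardless of a severe reaction, or that it has no safeguard beyond the individual. The documents do not support that: such a reaction may well lead to a 'not ok' judgement, and the discretionary powers exist.

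**Conclusion.** The point holds in limited form. The stated hold after a severe or life-threatening site reaction is confined to the affected subject, and the hold after a related systemic Grade 3 or 4 reaction most naturally reads the same way. In the visible text, nothing makes others at that dose, or the start of the next level, wait for a consultation that the protocol already requires. This is more than an omitted detail, because a hold rule is stated and is too narrow for a new route and adjuvant.

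The first-cohort ranges of 0 to 2 doses at 80 µg, and 0 to 4 after an adjuvant-only event, are illustrative. They depend on unstated start dates and consultation length. The exposure of the next level, from a reaction after the two-week evaluation, is not quantified. Confidence is moderate, because the unseen figure could close the escalation half of the gap.

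**What to change.** In section 5.4.1, complete the damaged sentence on systemic reactions and add that, after either type of event, if judged at least possibly related:

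- further dosing at the affected dose level pauses, and the next level does not start, until the supplier consultation is completed and documented;
- if the event is in an adjuvant-only subject, the suppliers and the investigator decide in that same consultation whether the other Endocine arms pause;
- any pause is applied to concurrently dosed subjects without disclosing allocation.

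The relatedness condition uses the causality assessment that section 9.1.4 already requires for every adverse event.

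In section 4.1, state that 'ok' requires no such consultation to be outstanding, at every dose level, and that this includes reactions occurring after the two-week evaluation. If the escalation figure already says so, a cross-reference is enough for that part.

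In section 11.3, state that a dose delayed by such a hold is not by itself a major protocol violation.

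The cost is a short amendment using existing triggers, contacts and the 24-hour notice, with no new committee or data collection. The downside is a possible short pause that may shift a weekly dose. A dose missed altogether would still fail the full-immunization condition of the per-protocol set, which is a further reason to complete the consultation quickly.

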## Rationale for study design and treatment regimens

Previous studies have shown that intra-dermal immunization with Vacc-4x using GM-CSF as adjuvant gives an immunological response that is believed to be essential to control HIV better. This study is a pilot study to investigate if intra-nasal administration is a possible administration rout.

# Selection and withdrawal of subjects

## Subject screening, enrollment, and identification log

A subject screening log will be completed at the investigational site for all subjects who were considered for the study but not enrolled and subject screening/enrollment and subject identification logs will be completed for subjects enrolled in the study.

## Inclusion criteria

A subject will be eligible for enrollment in the study if all of the following criteria apply:

- Age above 18 years, both genders.
- HIV positive at least one year.
- Clinically stable on ART for the last 6 months (changes in therapy is allowed as long as the viral load is stable).
- Documented viral load (HIV-1 RNA) less than 50 copies/mL for the last six months.
- Documented stable CD4 cell count ≥ 400x106/L.
- Nadir (lowest ever) CD4 cell count ≥ 200x106/L.
- Signed informed consent.

## Exclusion criteria

A subject will not be eligible for this study if any of the following criteria apply:

- Reported pre-study AIDS-defining illness within the previous year (see Appendix 16.2).
- Malignant disease.
- On chronic treatment with immunosuppressive therapy.
- Unacceptable values of the hematologic and clinical chemistry parameters, as judged by the Principle Investigator (or designee), including creatinine values >1.5x upper limit of normal (ULN), and AST (SGOT), ALT (SGPT) and alkaline phosphatase values >2.5x ULN.
- Concurrent chronic active infection such as chronic viral hepatitis B or C or active tuberculosis.
- Pregnant or breastfeeding women.
- Women of childbearing potential not using reliable and adequate contraceptive methods (defined as: use of oral, implanted, injectable, mechanical or barrier products for the prevention of pregnancy; practicing abstinence; sterile) during the study, or sexually active male patients with partners of childbearing potential unwilling to practice effective contraception during the study.
- Current participation in other clinical therapeutic studies.
- Incapability of compliance to the treatment protocol, in the opinion of the Investigator.

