16.2 AIDS-Defining Illnesses [51](#__RefHeading___Toc289425612)

List of Abbreviations

| **Abbreviation** | Definition/Term |
| --- | --- |
| AE | Adverse Event |
| AIDS | Acquired Immunodeficiency Syndrome |
| ALT | Alanine Transaminase (SGPT) |
| ALP | Alkaline Phosphatase |
| ART | Antiretroviral Therapy |
| AST | Aspartate Transaminase (SGOT) |
| CRF | Case Report Form |
| CRP | C-reactive Protein |
| DTH | Delayed type Hypersensitivity |
| EDTA | Ethylenediamine Tetra acetic Acid |
| ELISPOT | Enzyme-linked Immunosorbent Spot Assay |
| EU | European Union |
| Eur Pharm | European Pharmacopoeia |
| -GT | Gamma Glutamyl Transferase |
| GCP | Good Clinical Practice |
| GM-CSF | Granulocyte Macrophage Colony Stimulating Factor |
| GMP | Good Manufacturing Practice |
| HIV | Human Immunodeficiency Virus |
| HLA | Human Leukocyte Antigen |
| ICF | Informed Consent Form |
| ICH | International Conference on Harmonization |
| IEC | Independent Ethics Committee |
| IMP | Investigational Medicinal Product |
| IND | Investigational New Drug |
| LD | Lactate Dehydrogenase |
| MedDRA | Medical Dictionary for Regulatory Activities Terminology |
| PBL | Peripheral Blood Lymphocyte |
| PI | Principal Investigator / Sponsor |
| SAE | Serious Adverse Event |
| SOC | System Organ Class |
| Th1 | T-helper Cell Type 1 |
| Th2 | T-helper Cell Type 2 |
| ULN | Upper Limit of Normal |
| USP | United States Pharmacopoeia |
| WBC | White Blood Cells |
| WFI | Water For Injection |
| WHO | World Health Organization |
|  |  |
|  |  |

Protocol Synopsis

| Protocol Title: | | IMMUNOTHERAPY OF HIV-INFECTED PATIENTS  A single-blinded, randomized, immunogenicity, pilot study of intranasal administration of Vacc-4x with Endocine as adjuvant. | | |
| --- | --- | --- | --- | --- |
| Protocol Number: | | CT -BI-Vacc-4x/L3-2011/1 | | |
| **Name of Sponsor & Investigatio­nal Drug Substance Suppliers:** | Sponsor/Investigator: [name], Oslo University Hospital  Vacc-4x: Bionor Pharma ASA, [name]  Eurocine adjuvant: Eurocine Vaccines AB, Karolinska Institutet Science Park, [name] | | | |
| Drug Substance: | Vacc-4x: A formulation of four synthetic peptides (Vacc-10, Vacc-11, Vacc-12, and Vacc-13).  Endocine adjuvant: A lipid based nano-emulsion consisting of mono-olein and oleic acid in 0.15 M NaOH at pH 8.0. | | | |
| Investigational Drug Product: | Vacc-4x with Endocine adjuvant | | | |

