## Clinical Studies

Four clinical studies have been conducted with Vacc-4x; a Phase I clinical study at the University of Bergen, Norway including 11 patients, and a Phase II clinical study at Ullevål University hospital in Oslo, Norway that enrolled 40 chronic HIV‑infected patients ([Åsjö, 2002;](#Åsjö2002) [Kran, 2004](#Kran2004)). In a follow-up of the patients at former Ullevål university hospital 7 years after immunization, most patients who earlier had responded to Vacc-4x now showed detectable CD4 memory cells which could be activated (Report CTN-BI/Vacc-4x/2009/1 2011-02-02). In addition, one phase II study has just been finished, i.e. a randomized, double-blind, multicenter, immunogenicity study of Vacc-4x versus placebo in patients infected with HIV-1 who have maintained an adequate response to ART (EudraCT Number 2007-006302-13). This study included 135 patients. In this study no effects on CD4 counts was seen but there was a favorable effect on viral load.

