### Prohibited medications

Subjects are prohibited from concomitant use of any of the following medications:

- Any other immunomodulating therapy
- Chronic corticosteroids, except for asthma inhalers or topical use
- Other investigational drugs, agents, or devices

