## Efficacy assessments

### Delayed type hypersensitivity test administration

DTH testing will be performed at the last visit (Week 8). An injection of 0.1mL of a 4.0mg/mL Vacc‑4x should be administered intradermally at the front of left arm. The DTH test should be performed by the investigator, study nurse, or other clinician experienced in the techniques of intradermal injection. The DTH test results will be evaluated 48 hours after the tests are performed. For each DTH test, evaluation of the injection site at 48 hours will include palpable skin induration and skin erythema. A positive DTH test is defined as an area 10mm2 (either induration or erythema). Study personnel will record DTH results in the subject’s source documents and transcribe them into the CRF. For subjects whose DTH reactions are measured by someone other than study personnel, the investigator is responsible for collecting and recording the result; use of a prepared form completed by the alternative evaluator at the time of the reading is strongly recommended and should be filed with the subject’s source documents.

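### Nothing in the protocol keeps previous Vacc-4x recipients out, and the week 8 DTH result, which has no baseline, could not be read as a response to intranasal dosing in such a subject

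*Protocol*

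**What the plan says.** **Eligibility.** The inclusion list (Section 5.2), the exclusion list (Section 5.3) and the synopsis do not mention earlier Vacc-4x. The nearest criterion is "Current participation in other clinical therapeutic studies". Section 6.2.2 opens with "Subjects are prohibited from concomitant use of any of the following medications", so it does not reach back to a past immunization.

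**Earlier exposure.** Section 2.4 lists "a Phase II clinical study at Ullevål University hospital in Oslo, Norway that enrolled 40 chronic" HIV-infected patients, and reports that 7 years after immunization there "most patients who earlier had responded to Vacc-4x now showed detectable CD4 memory cells which could be activated". It also describes a Phase I study of 11 patients in Bergen and a recently finished multicentre, placebo-controlled study: "This study included 135 patients".

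**Setting.** Section 4.1 calls the trial single centre. The synopsis places the sponsor/investigator at "Oslo University Hospital".

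**Endpoints.** DTH is tested only at week 8 (Sections 6.1.2, 7.3.3 and 8.2.1) and is positive at an area of at least 10 mm² (Section 3.2.2). Section 3.1.2 sets it against patients on effective ART who had not been vaccinated, taken from a preceding study. T-cell response is measured at screening and week 1 as well as at week 8. Section 11.6.3 analyses continuous endpoints by ANCOVA with the baseline value in the model. Section 11.2 names no stratification factor.

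**The concern.** The cellular-response objectives ask whether the intranasal product produces a response to Vacc-4x. In a subject already immunized by another route, a response at week 8 may be recall of memory laid down years earlier. The protocol itself supplies the evidence that such memory can persist.

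For DTH, nothing measured before dosing separates the two. The comparator in Section 3.1.2 makes sense only if the trial subjects had themselves not received Vacc-4x before this study, yet no criterion requires that. Against this external group, a previously immunized subject can only push the positive rate up. Between the randomized arms the direction depends on where the subject falls: a recall-positive subject in a Vacc-4x arm inflates the apparent effect, and one in the adjuvant-only arm masks it.

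**Working it through.** **1. The plan's own figure.** 4 arms × 6 subjects = 24, as stated. No power calculation is given (Section 11.1), so the check concerns what one subject can do to an arm of six.

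**2. Does any provision close the gap?**

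| Provision | Reaches earlier Vacc-4x? |
|---|---|
| Section 5.3, participation in other studies | No, current participation only |
| Section 5.3, investigator's opinion | No, concerns compliance |
| Section 6.2.2, prohibited medications | No, concomitant use only |
| Sections 7.3.1, 8.1 and 8.3.1, medical and medication history | May reveal it, but does not act on it |
| Section 11.2, randomization | No stratification by it |

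**3. Does any measurement correct for it?**

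| Endpoint | Pre-dose value | Adjustment |
|---|---|---|
| DTH | None | None available |
| T-cell response | Screening and week 1, both mandatory (Table 2, note on T-cell sampling) | Change from baseline; ANCOVA on baseline |

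The T-cell baseline would show strong existing memory and partly adjust for it. It would not say whether a later rise is boosted recall or a new response.

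**4. Largest shift in one arm's DTH-positive rate.** One recall-positive subject: 1/6 = 16.7 percentage points. Two: 2/6 = 33.3 points. These are ceilings. They require that the previously immunized subject is positive and that the person who would otherwise have held the place is negative.

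**5. Would randomization balance it?** Assume k previously immunized subjects among 24, allocated at random with six per arm. This ignores the stepwise start in Section 4.1. P(at least one in the adjuvant-only arm) = 1 − C(24−k, 6)/C(24, 6).

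| k (assumed) | At least one in the adjuvant-only arm | Some arm has two or more |
|---|---|---|
| 1 | 25% | 0% |
| 2 | 45% | 22% |
| 3 | 60% | 57% |
| 4 | 71% | 88% |

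For k = 2: 1 − (18/24)(17/23) = 1 − 306/552 = 0.446.

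**6. Illustration with invented counts.** Two-sided Fisher exact test, which is not the test planned in Section 11.6.3 (Cochran-Mantel-Haenszel):

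- 5/6 v 0/6 gives p = 0.015. One recall-positive subject in the adjuvant-only arm makes it 5/6 v 1/6, p = 0.080.
- 4/6 v 0/6 gives p = 0.061. One recall-positive subject replacing a negative in the Vacc-4x arm makes it 5/6 v 0/6, p = 0.015.

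These show how sensitive arms of six are. They do not predict a result.

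**The case against.** The case on the other side has real weight.

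- **Contamination is not shown.** The documents do not say that earlier recipients will be approached. A reader might add up the earlier studies, 11 + 40 + 135 = 186, and infer a pool much larger than the 24 needed. That does not follow. The 11 were in Bergen, the 135 were multicentre and included placebo, and neither the Oslo share nor the Vacc-4x share is given. Only the 40-patient study is clearly tied to Oslo, and those patients would still have to meet the CD4, nadir and viral-load criteria. This stands, and k in the working is an assumption.
- **T-cell endpoints have baselines.** A reader might infer that all immunogenicity results are equally exposed. They are not: two pre-dose measurements and the ANCOVA would reveal and partly absorb existing memory. A high pre-dose T-cell value could also help flag a subject when DTH is interpreted. This stands, and it confines the main problem to DTH.
- **The persistence evidence is narrower than DTH.** Section 2.4 speaks of most earlier responders, not all recipients, and of CD4 memory cells, not skin tests. Section 2.6 also speaks of boosting p24 responses, and every subject is HIV-infected, so a clean contrast of naive priming with recall is not available in anyone. This stands as a limit on size. It does not supply the missing DTH baseline.
- **It is a safety pilot.** The primary objective is safety and the efficacy analysis is chiefly descriptive. This limits the harm to secondary endpoints. A descriptive rate out of six is still misleading if one of the six was immunized before.

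History-taking could record earlier vaccination, and a summary without such subjects is ordinary analysis-plan material. Eligibility, however, is settled in the protocol.

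**Conclusion.** The point holds, mainly for DTH. Followed as written, the criteria admit people who have already received Vacc-4x, and their single week 8 skin test could not be attributed to intranasal dosing in any arm. Each such subject could move an arm's DTH-positive rate by up to 16.7 percentage points. The T-cell endpoints are affected to a lesser degree.

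The conclusion rests on three things: the criteria as printed, the 7-year memory finding in Section 2.4, and the absence of a baseline DTH. It assumes that persisting CD4 memory can show as a positive skin test, which the protocol does not document. The number of subjects concerned is unknown and may be zero, so the documents do not support a claim that the results will be distorted. The safety objective is not touched by this argument.

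**What to change.** Add one line to Section 5.3 and to the synopsis: *Previous receipt of Vacc-4x.* Add a screening question on earlier participation in a Vacc-4x trial, recorded on the CRF. The evidence cited concerns Vacc-4x only and does not by itself justify extending the exclusion to every HIV therapeutic vaccine.

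If a previous recipient is already enrolled, flag that subject and repeat the DTH summaries, and the T-cell summaries, without them.

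The cost is small: a slightly smaller recruitment pool and one extra question. The sample size stays at 24, six per arm.
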